## Abstract

**Background:**

Individuals taking oral anticancer agents (OAAs) often face important challenges, requiring more timely informational support, ongoing monitoring, and side effect management.

**Objective:**

This study, guided by the Self-Efficacy Theory, aims to assess the feasibility, acceptability, and potential effects of a comprehensive, digital OAA intervention.

**Methods:**

A 2-arm, mixed methods, pilot randomized controlled trial took place at a large university-affiliated cancer center in Montreal, Quebec, Canada. Participants (N=52) completed baseline self-report e-questionnaires and subsequently were randomly assigned to the experimental group (intervention plus usual care, n=26) or control group (usual care only, n=26). The study intervention, designed to increase medication adherence via medication adherence self-efficacy and decreased symptom distress, included (1) OAA informational videos, (2) OAA-related e-handouts and other supportive resources, (3) nurse-led follow-up calls, and (4) e-reminders to take OAAs. The e-questionnaires were completed once a week for the first month and every 2 weeks for the subsequent 4 months, or until OAA treatment was completed. A subset from both groups (n=20) participated in semistructured interviews once they completed the study requirements. Study feasibility is assessed using recruitment, retention, and response rates, as well as intervention uptake. Through e-questionnaires and exit interviews, intervention acceptability is to be assessed prospectively at baseline and retrospectively upon study completion. Potential effects are then assessed via medication adherence self-efficacy, medication adherence self-report, and symptom distress.

**Results:**

Data collection was completed by December 2023 with a final sample size of 41. Results are expected to be published in 2025.

**Conclusions:**

This study relies on a theoretically based, OAA digital intervention with modalities tailored to the needs and preferences of participants. The use of quantitative and qualitative methods enriches our understanding of the potential contributions of the intervention. In addition, following participants over the course of treatment captures potential changes in oral treatment–related processes and outcomes.

**Trial Registration:**

ClinicalTrials.gov NCT04984850; https://www.clinicaltrials.gov/study/nct04984850

**International Registered Report Identifier (IRRID):**

DERR1-10.2196/55475

## Introduction

### Background

It is estimated that 18.1 million new cancer diagnoses occur globally every year [1,2]. Whereas survival rates vary among cancer diagnoses and countries, mortality rates for the most prevalent cancers in high-income countries continue to decrease [2,3]. Individuals with cancer are living longer and with higher quality of life due to improvements in prevention, detection, and advancements in treatment [4]. More specifically, driven by cost-effectiveness, patient convenience, and the potential for improved patient outcomes, the use of orally administered anticancer drugs continues to grow. It is now estimated that 60% of all new cancer medications currently in development are oral, across all cancer types and stages [5].

Oral anticancer agents (OAAs), having grown in popularity in the past few years, demonstrate equivalent efficacy, safety, and outcomes as intravenous chemotherapy, while being less invasive and easier to administer [6]. As OAAs are taken at home rather than in cancer centers or hospitals, medication management resides with patients- requiring them to be active in their care [7]. For OAAs to be as effective as possible and demonstrate outcomes equivalent to those seen in clinical trials, patients must follow best practices for their treatment, resulting in added responsibilities for medication management [8]. These include attention to treatment adherence, as well as monitoring and management of side effects and adverse events, especially at OAA treatment onset when side effects and toxicity may be high [9,10]. However, the literature to date suggests that patients often report having unmet OAA-related needs, feeling helpless at home, receiving insufficient knowledge and support to manage their treatment, and having suboptimal medication adherence [10-13].

A Canadian survey conducted among individuals treated for cancer in the last 6 months (N=3300), for instance, found that only 62% of individuals on OAAs reported receiving information and guidance on potential side effects and how to manage them, compared to 74% for radiation and 76% for intravenous chemotherapy. In the same sample, only 67% of individuals on OAAs felt their care provider did everything they could to help with side effects, compared to 73% for radiation and 76% for intravenous chemotherapy [14]. Elsewhere, the lack of OAA information and monitoring for side effects were found to be significantly related to fatigue, nausea and vomiting; change of taste; and poorly managed mouth sores [15].

Medication adherence, the extent to which a person’s medication-related “behavior corresponds with agreed-upon recommendations from their health care provider” [16], denotes a collaborative relationship between the health care provider and patient where the patient plays an active role in taking their prescribed treatment [17]. Medication adherence is construed as one of the primary determinants of treatment success, as unwanted alterations in dose and timing affect treatment-related outcomes [18,19]. However, medication adherence rates for OAAs vary significantly, with a systematic review across 63 studies reporting adherence rates ranging from 46% to 100% [20]. Lower OAA adherence is found to be related to decreased treatment effectiveness, increased health care utilization, and increased costs due to more physician visits, higher hospitalization rates, longer hospital stays, and in some cases, decreased survival [21-24].

As OAA development and use expands, medication adherence issues related to OAAs are increasingly of interest to multiple stakeholders, including policy makers, insurance companies, drug makers, health care providers, and researchers [25]. A systematic review of factors influencing adherence to oral anticancer drugs identified three potentially modifiable factors that interventions should address: (1) side effects and toxicities, (2) forgetfulness, and (3) the lack of timely information [26]. The American Society of Clinical Oncology and the Oncology Nursing Society jointly released evidence-based guidelines and OAA management standards. These emphasize patient education at OAA initiation and ongoing monitoring throughout treatment to enable early identification of side effects and toxicities, thus preventing complications [27,28]. Consequently, there is a need for more timely and more accessible patient support for individuals taking OAAs [28].

A comprehensive, personalized, digital OAA intervention was developed based on Bandura’s [29] “Self-Efficacy Theory.” One of the intervention goals is to increase medication adherence by increasing medication adherence self-efficacy (SE) and symptom distress. SE refers to individuals’ beliefs in their own ability to successfully perform a specific task related to specific behavior, for instance, remembering to take medication on time to adhere to treatment, or effectively self-managing fatigue experienced from treatment [29,30]. A systematic review of the relationship between SE and medication adherence found a positive link between these two variables in 59 out of the 66 studies reviewed [31]. Behavior is influenced by the interaction between perceived SE and expectations surrounding the outcome of the behavior; thus, medication adherence is affected by a patient’s belief in their capacity to consistently remember to take medication and the belief that consistently taking the medication, as prescribed, will be an effective treatment to kill cancer cells in their body. Knowledge and self-management skills of disease care can enhance SE through expectations [32]. In support of this, a standardized patient education and follow-up intervention for oral chemotherapy by Tokdemir and Kav [33] successfully increased medication adherence SE after the intervention (66.39 vs 71.04; *P*<.05). Herein, we tested a broader multimodal intervention that went beyond patient education.

### Purpose of Study

The aim of this pilot randomized controlled trial (RCT) was to document the feasibility and acceptability of the experimental intervention. Pilot studies are critically important as a first step to address practical, logistical, and methodological issues that may arise. In addition, this pilot RCT seeks to determine whether study components can be executed and delivered to participants as planned and the intervention’s potential impact on medication adherence SE, adherence, and symptom distress among participants on OAAs.

More specifically, the study’s first aim was to establish feasibility, defined as “whether the intervention, study design, and procedures can be successfully executed by the researcher and delivered to the participants as planned” [34]. The constructs of feasibility herein include participant recruitment, retention, self-report questionnaire response, and uptake of the intervention. Predetermined objectives and measures of success for each are reviewed in the *Methods* section while Figure 1 provides an overview.

**Figure 1 figure1:**
[figure not shown]
Study aims, objectives, and measures.

The second aim is to determine the acceptability of the intervention. The definition and measures of acceptability are based upon theoretical framework of acceptability of health care interventions by Sekhon et al [35], which defines acceptability as a multifaceted construct reflecting the appropriateness of the intervention. A key feature of this framework is the distinction between prospective, concurrent, and retrospective acceptability, emphasizing that acceptability can be assessed before, during, and after the intervention as all 3 can have an impact on participant use and access to the intervention. Although Sekhon et al [35] propose 7 concepts of intervention acceptability, only the 3 most relevant are included herein, namely intervention burden, coherence, and perceived effectiveness.

The third aim of the study focuses on documenting the potential effects of the intervention: As stated in the CONSORT (Consolidated Standards of Reporting Trials) on randomized pilot and feasibility trials [36], pilot trials may assess potential effectiveness using surrogate outcomes—substitute measures used as alternatives to clinical outcomes that may be challenging to assess directly [36]. Herein, potential intervention effects are assessed by comparing experimental and control groups over time, from baseline, every 2 weeks (depending on the outcome), and after the intervention. It is hypothesized that over time, compared to the control group, the experimental group will report higher medication adherence SE, higher medication adherence, and lower overall symptom distress.

## Methods

### Design

A prospective, mixed methods, 2-arm, pilot RCT is being conducted to address the study aims and hypothesis.

### Setting

The study takes place at a large academic cancer center in a university-affiliated hospital in Montreal, Quebec, Canada.

### Ethical Considerations

The study received approval from the Psychosocial Research Ethics Committee of CIUSSS West-Central Montreal Research Ethics Board (Project 2021-2861). Participants provided written informed consent. A randomly generated unique number (combination of numbers containing no identifiers) was generated and assigned to each participant such that all data collected were deidentified. As a token of appreciation for the time spent completing study e-questionnaires at baseline and follow-ups, participants received a CAD $10 (a currency exchange rate of CAD $1=US $0.69 is applicable) gift card at baseline as well as an additional one for each set of e-questionnaire completed. In sum, each participant could receive a maximum of CAD $120 in gift cards over the 5-month study period. If they withdrew from the study at any time, they receive a minimum of CAD $10 for the baseline e-questionnaire with an additional CAD $10 for each follow-up e-questionnaire completed.

### Sample

A sample of 52 participants (26 per arm) was to be recruited and randomly assigned, at any moment from the decision to start OAA therapy to the completion of their first oral medication cycle.

#### Sample Size

Sample size calculation was undertaken using procedures provided by the software program G*Power 3 [37]. As per our statistical consultant, the calculation was undertaken to determine adequate power in the determination of the potential effects of the intervention (aim 3), in which a repeated-measures ANOVA with a within-between interaction would be the statistical test used. The parameters for the power calculation included an effect size of 0.25 (standard medium effect size for ANOVA) [38], α of .01, and a power of 0.95. The sample size was further increased to account for a 30% attrition rate over the study duration, determined to be appropriate given a review of attrition rates in supportive oncology trials found a mean of 26% (95% CI 23%-28%) across 18 trials (ie, the original sample size was 36, total with added 30%, attrition is 52) [39].

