### Data Collection

In both groups, follow-up e-questionnaires were completed every week for the first month and 2 weeks for the following 4 months, or until treatment was completed (if less than 5 months). Given the considerable variability in the duration of time patients may remain on OAAs, the study duration of 5 months was established as a long enough period in consultation with medical oncologists and pharmacists and was deemed appropriate for assessing the primary outcomes of feasibility and acceptability. Participants were monitored more closely during the first treatment cycle, as this period is critical for identifying potential toxicities and making necessary dosage adjustments. Furthermore, it is crucial to establish positive medication adherence behaviors early in the treatment process [46]. After 5 months or until OAA treatment was completed (if less than 5 months), participants completed the exit questionnaire, and a subset of participants in the experimental group (n=10) and control group (n=10) who had completed the study were invited to participate in a semistructured interview.

All e-questionnaires were completed on Qualtrics, a secure web-based electronic data capture system licensed through McGill University [47]. A data management plan between the university and the affiliated hospital was established for the study (Multimedia Appendix 1). Details of each measure and timepoint are provided in Table 1.

Baseline questionnaires completed by all participants included sociodemographic and medical characteristics, cancer information-seeking preferences, and OAA knowledge.

**Table 1 table1:** Study data collection.

Objective and measure			Instrument		Items, n		Time of collection				
						Baseline		Weekly for the first cycle	Every 2 weeks for cycles 2-5	Final questionnaire	Study completion

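### The 0.95 power is for a medium f on the group-by-time interaction, which means an arm difference changing by at least 1 SD; power for a 0.5 SD difference is far lower unless repeated scores correlate very highly

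*Protocol article*

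**What the plan says.** The Sample Size section says the calculation was made to give adequate power for the potential effects of the intervention (aim 3), and that "a repeated-measures ANOVA with a within-between interaction would be the statistical test used". The inputs are "an effect size of 0.25 (standard medium effect size for ANOVA" and "α of .01, and a power of 0.95". The result is that "the original sample size was 36, total with added 30%, attrition is 52".

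Purpose of Study sets the hypothesis: over time, compared with control, "the experimental group will report higher medication adherence SE, higher medication adherence, and lower overall symptom distress". Data Collection gives the schedule: "follow-up e-questionnaires were completed every week for the first month and 2 weeks for the following 4 months". Data Analysis applies repeated-measures ANOVA to MARS-5, MASES and ESAS-r. Results reports a final sample of 41 (23 experimental, 18 control).

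**The concern.** The paragraph takes a benchmark that describes a 0.5 SD difference when two group means are compared, and applies it to an interaction over many occasions. There the same value of f describes a much larger difference between arms. A reader who sees 0.95 power next to a standard medium effect will take the trial to be well placed to detect a medium difference, and will tend to read a nonsignificant interaction as evidence against one. The Discussion says the interviews will give context for significant or nonsignificant outcomes, and the Conclusion looks ahead to a multisite study. Either use would carry the misreading forward.

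**Working it through.** **Inputs.** From Sample Size: f = 0.25, alpha = .01, power 0.95, N = 36, attrition 30%. Two groups. From Data Collection: about 4 weekly plus 8 two-weekly follow-ups, so 12, or 13 with baseline. The gift-card maximum under Ethical Considerations (CAD 120 at CAD 10 each) implies 12 sets including baseline. Not stated: the number of occasions m used in the calculation, the correlation rho between occasions, and the sphericity factor eps. I assume the G*Power defaults (rho 0.5, eps 1) and then vary rho.

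**1. Reproducing 36 and 52.** For this test lambda = f² × N × m × eps/(1 − rho), df1 = (m − 1)eps, df2 = (N − 2)(m − 1)eps. With m = 6, lambda = 0.0625 × 36 × 6/0.5 = 27.0 on 5 and 170 df, and power is 0.951. N = 34 gives 0.934. So 36 reproduces, and 36/0.7 = 51.4, rounded up to 52, is right.

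**2. Number of occasions.** At the defaults, 12 or 13 occasions would need only N = 24 or 22, and power at N = 36 is 0.999 or more. Exactly 36 also arises at m = 12 with rho 0.19 to 0.23, at m = 13 with rho 0.15 to 0.19, and at m = 13 with rho 0.5 and eps 0.5.

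**3. What f = 0.25 means here.** Let d_j be the arm difference at occasion j in outcome SDs. With two equal groups the interaction effects are ±(d_j − mean d)/2, so f = SD(d_j)/2, and f = 0.25 means SD(d_j) = 0.5.
- Any pattern: values spanning a range R have an SD of at most R/2, so R is at least 1.0 SD.
- Step to D straight after baseline: SD = D√(m − 1)/m, which is 0.373D, 0.276D and 0.266D at m = 6, 12 and 13. Hence D = 1.34, 1.81 and 1.88.
- Linear growth to D over evenly spaced occasions: SD = D√[(m + 1)/(12(m − 1))], which is 0.342D, 0.314D and 0.312D. Hence D = 1.46, 1.59 and 1.60.

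**4. Power for a 0.5 SD arm difference.** Now f = 0.25 × SD/D: 0.0932 (m = 6) and 0.0666 (m = 13) for the step, 0.0854 and 0.0780 for the line. Example: step, m = 13, N = 36, rho 0.5 gives lambda = 0.0666² × 36 × 13/0.5 = 4.15 and power 0.069. Ranges at alpha .01 over both patterns, m = 6, 12 and 13, and N = 36 and 41 (treated as balanced):

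| rho | power |
|---|---|
| 0.2 | 0.04–0.07 |
| 0.5 | 0.07–0.13 |
| 0.7 | 0.15–0.29 |
| 0.8 | 0.28–0.53 |
| 0.9 | 0.70–0.94 |

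Sensitivity to pattern: a line drawn on the actual calendar spacing gives up to 0.15 at rho 0.5, and 0.96 at rho 0.9 in one setting (13 occasions, N = 41). A 0.5 SD difference that appears only for the second half of the occasions has f = 0.125. Its power is 0.24 to 0.51 at rho 0.5 (6 to 12 occasions), and it passes 0.95 by rho 0.8 at 12 occasions.

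**5. What 23 versus 18 delivers as estimation.** √(1/23 + 1/18) = 0.315 and t is about 2.02. The half-width for a single-time difference is 0.315 × 2.02 = 0.64 SD. For the baseline-adjusted mean of 12 follow-ups at rho 0.5, the variance is (1 + 11 × 0.5)/12 − 0.5² = 0.292, whose root is 0.540, and the half-width is 0.64 × 0.540 = 0.34 SD.

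**The case against.** The arithmetic does not fail: 36 and 52 both reproduce. The text labels f = 0.25 as medium for ANOVA and nowhere promises power for a 0.5 SD arm difference. Feasibility and acceptability are the primary outcomes, aim 3 concerns potential effects, the Conclusion concedes a small sample, and data collection is over. With very high correlation, power for 0.5 SD is respectable. All of this is fair. It limits the point to how the power statement is worded and read.

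A reader might also infer that 36 is wrong because the defaults give it at 6 occasions while about 12 to 13 are scheduled. The document does not support that. It does not state m, rho or eps, other settings give 36 at 12 or 13 occasions, and baseline plus five cycles would itself make six. Nor does the mismatch lower power: at f = 0.25 and the defaults, more occasions raise it to 0.999. Leaving those three settings out is ordinary condensation in an article and is not the point here.

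What the objection does not answer is that the section calls the power adequate for aim 3 and pairs 0.95 with a medium label that, on this test, stands for a change of at least 1 SD.

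**Conclusion.** The point holds as a misdescribed effect size. The design has 0.95 power for an arm difference that changes by at least 1.0 SD, and by about 1.3 to 1.9 SD under a sustained step or steady divergence. It does not have it in general for a 0.5 SD difference: about 0.07 to 0.13 at rho 0.5, rising to 0.70 to 0.94 at rho 0.9, for those two patterns with evenly spaced occasions, sphericity and N = 36 to 41. Rho is an assumption throughout, and only very high correlation or a favourable time pattern brings power near 0.95. It would therefore be too strong to say that the test would almost always miss a medium effect, or that the stated power fails for the f that was entered.

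**What to change.** Keep N. In the Sample Size section, replace the claim of adequate (0.95) power for a medium effect with two statements:
- f = 0.25 on the interaction corresponds to an arm difference changing by at least 1.0 SD over time (1.34 to 1.88 SD for a sustained step, 1.46 to 1.60 SD for linear divergence, at 6 to 13 occasions);
- power for a 0.5 SD arm difference is well below 0.95 unless the correlation between occasions is very high.

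Present aim 3 as estimation with 95% confidence intervals, giving the expected half-widths at 23 versus 18 (about 0.64 SD at a single time, about 0.34 SD for the baseline-adjusted follow-up mean at rho 0.5). Say that a nonsignificant interaction is not evidence against a medium effect. The cost is one reworded paragraph and a less favourable power statement. No patients are added.

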#### Inclusion Criteria

The inclusion criteria were as follows: being 18 years or older; being seen at the study cancer center; having a diagnosis of cancer at any stage; and being about to start or within the first cycle of oral anticancer treatment (traditional cytotoxic, targeted therapy, or hormonal therapy as adjuvant treatment). Potential participants had to have access to a computer tablet or smartphone device with internet, as well as the ability to communicate, read, and write in English or French.

#### Exclusion Criteria

The exclusion criteria were as follows: receiving intravenous chemotherapy, immunotherapy, or oral hormonal therapy as long-term maintenance treatment for the prevention of cancer’s return or growth of cancer cells after initial treatment, assisting in prolonged remission; any significant physical or cognitive limitations that would prevent the ability to fully participate in the study (as reported by the patient, primary health care provider, or research staff); and being at imminent “end-of-life,” defined as a condition in rapid decline whereby active treatment is stopped and considered in the actual process of dying [40]. We also excluded patients who were already participating in an ongoing clinical trial.

